#### Monitoring treatment fidelity for the MINT intervention

Fidelity to the intervention protocol is an important consideration for complex interventions. Using the expanded Lichenstein treatment fidelity model developed by the OBSSR Behavior Change Consortium
[48,49], we will ensure fidelity through training and ongoing fidelity monitoring. At the beginning of the study, research assistants will participate in an intensive training that consists of the basic physiology of blood pressure, instruction on proper measurement of blood pressure, a primer on behavioral principles of the intervention, and basic interview skills taught through role playing and didactic teaching. In addition, research assistants will receive two full days of information on the principles of MINT techniques, and practice in the delivery of MINT via role-playing. The interventionists will meet biweekly to discuss the previous week’s sessions, troubleshoot, problem-solve and plan for the following week. Bi-monthly booster sessions will be conducted to minimize drift in MINT counseling skills.

All individual MINT sessions will be digitally audio-taped and used for two purposes: 1) individual counselor development and ongoing training/supervision; and 2) systematic review for treatment fidelity. The relatively immediate review and use of recordings will facilitate the feedback and coaching process to develop and maintain the skills of the trained counselor, an approach that has proven to be effective in previous MINT studies
[43]. The audio files will also be archived for systematic sampling of a third of participant’s first session and another randomly selected session for adherence to MINT principles as scored by the Motivational Interviewing Treatment Integrity (MITI) scale
[50], a validated instrument with satisfactory reliability, convergent and discriminative validity
[51].

#### Patient navigation intervention

This intervention will be patterned after the standard New York City Department of Health and Mental Hygiene (NYC DOHMH) patient navigation (PN) protocol
[52], and culturally-targeted to black men. It is widely accepted in the health promotion literature that interventions are more effective when they are culturally appropriate. Thus, the effect of a CRC screening navigation intervention in black men may be improved by enhancing its cultural appropriateness through cultural targeting, defined as the use of “a single intervention approach for a defined subgroup that takes into account characteristics shared by the subgroup’s members”
[23]. This can be achieved via several approaches
[53] that are particularly relevant to CRC screening navigation: 1) an evidential approach that focuses on the impact of a given health issue on the target group through data, including incidence, prevalence or mortality rates; 2) a linguistic approach that focuses on using the preferred language of a specific group; and 3) a sociocultural approach that addresses health-related issues in the context of broader social and cultural values and characteristics of a group. Compared to standard or “generic” interventions, culturally targeted interventions are rated more favorably, are perceived as more credible, and result in greater retention of knowledge over time and greater adherence to recommended health behaviors
[54-57].

The goals of the intervention will be to 1) educate participants about CRC screening tests; 2) address participants’ concerns about CRC screening; and 3) help participants overcome barriers to screening (Table 
2). Participants randomized to this arm will receive at least two planned sessions with trained patient navigators (PN) to assist them with completion of their choice of CRC screening modality. The first session will occur within seven days of enrollment, and will include culturally-targeted education about 1) CRC in African Americans, 2) risk factors and symptoms of CRC, 3) the need, eligibility and timeline for CRC screening, and 4) the different screening modalities. All participants will be given the American Cancer Society Colon Cancer DVD and Prevent Cancer Foundation Colon Cancer pamphlet. According to consensus guidelines, the main goal of CRC screening should be cancer prevention, and thus, structural examinations like colonoscopy are the screening tests of choice when the resources are available to an individual willing to undergo an invasive test. If participants are unwilling to undergo an invasive test or resources are not available, annual screening with high-sensitivity stool-based tests, like the fecal immunochemical test (FIT) card, is an acceptable option for colorectal screening in average risk adults aged 50 years and older
[58].

The initial session will primarily address the financial, structural and psychological barriers to CRC screening completion. After assessing the participant’s commitment to CRC screening, the navigator will refer the participant to the appropriate hospital, and/or will review the FIT completion process and mail three-day Hemoccult® ICT cards to those who request them. The navigator will encourage participants to schedule their colonoscopy appointment within one month or to return the completed FIT cards for testing within two weeks. In the case of colonoscopy, the second session will occur one week before the scheduled appointment, during which the navigator will review bowel preparation information and discuss potential barriers to attending the colonoscopy appointment (that is, obtaining the bowel prep or securing an escort, a requirement for discharge at many medical centers). In the case of FIT, the navigator will call participants to confirm receipt of the FIT card and review the testing steps. A third session might be necessary to confirm colonoscopy completion or relay FIT card results. In the case of multiple participant barriers, the navigator will continue to contact the participant on a weekly basis throughout the six-month intervention until the barriers are resolved and CRC screening is completed.

#### Monitoring fidelity for the patient navigation intervention

As with the treatment fidelity outlined above for the lifestyle intervention, we will adopt the Behavior Change Consortium Treatment Implementation model
[48,49]. The patient navigation coordinator for the research team (someone with extensive case management experience) and a co-investigator ([name]) will conduct intensive navigator training over the course of two days, utilizing the Colonoscopy Patient Navigator Program Orientation Manual training manual from the New York City Department of Health (NYC DOHMH) Program for Cancer Prevention and Control
[52]. The main training goals will be: 1) education (colon cancer, statistics, CRC screening) and 2) outlining the role of patient navigators (appointment referrals and reminders).

The NYC DOHMH modules will be supplemented with strategies to culturally target the navigation protocol to black men. This component includes 1) an overview of CRC statistics specific to black men; 2) a review of known barriers to CRC screening in black adults; 3) application of the CEEP barrier counseling framework (Clarify-Empathize-Explain-Plan) used in previous work
[59]; 4) interactive exercises to increase proficiency; and 5) a review of intervention protocol and data collection procedures. Each navigator will also participate in a minimum of three individual, one-on-one skill-building sessions to increase their confidence and mastery; three hours of role plays to simulate realistic PN experiences; a minimum of two hours’ training on intervention documentation and database usage; and at least three hours of one-on-one follow-up training with the patient navigator coordinator. Finally, patient navigators will undertake 56 hours of formal community health worker training organized by the Community Health Worker Network of New York City.

All navigation sessions will be digitally audio-recorded and used for two related purposes: 1) ongoing training/supervision of navigators; and 2) review for treatment fidelity. Ten percent of recorded navigation sessions will be randomly selected and reviewed by the PN expert using a PN fidelity checklist adapted from the Patient Navigator Performance Checklist
[60] and informed by the Technology Model of intervention integrity monitoring
[61] If this review reveals drift in the intervention delivery protocol by navigators, individual training sessions will be conducted to review relevant areas of training and refine navigator skills through role-play and feedback.

### Outcome assessments

The primary outcomes will be 1) within-patient change in systolic and diastolic BP from baseline to six months and 2) CRC screening rates as determined by colonoscopy report from the primary care provider at six months. For a complete list of measures, please refer to Table 
1.

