#### Eligibility criteria

Uncontrolled HTN is defined in accordance with current consensus clinical hypertension guidelines (Seventh Report of the Joint National Committee on Prevention, Detection, Evaluation, and Treatment of High Blood Pressure (JNC-7)) as an average BP that fulfills criteria of systolic blood pressure (SBP) ≥130 or diastolic blood pressure (DBP) ≥80 mmHg for those with diabetes or chronic kidney disease, and SBP ≥135 or DBP ≥85 mmHg for all others
[15]. Criteria for CRC screening eligibility (based on multi-society consensus guidelines) include: 1) no colonoscopy in the last 10 years; 2) no flexible sigmoidoscopy, Digital Contrast Barium Enema or CT-colonoscopy in the last 5 years, or 3) no Fecal Immunochemical Test (FIT) or Fecal Occult Blood Test (FOBT) in the last 12 months. In order to be eligible for the study a man must 1) self-identify as black or African American, 2) be age 50 or over, 3) have uncontrolled HTN, 4) be in need of CRC screening, 5) have a working phone, and 6) be fluent in English. Participants will be excluded if they do not meet any of these criteria. Approximately 480 self-identified black men who meet eligibility criteria will be randomly assigned to one of the two study conditions.

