#### CRC screening

CRC screening will be measured primarily by self-report. At six-month follow-up, participants will be asked whether they had a colonoscopy or any other screening for colorectal cancer during the course of the study. As the study will be based in the community and not directly related to any specific CRC screening program, participants who report having had CRC screening and records of it will be requested from the health center. Participants will be asked to sign a medical release form at the time of informed consent to grant permission to the research team to obtain CRC screening reports.

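### The CRC screening primary outcome is defined in two inconsistent ways, and the colonoscopy-only wording would score completed FIT screens as failures

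*Protocol article*

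**What the plan says.** The protocol article describes the CRC primary outcome in two places.

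- Outcome assessments: "CRC screening rates as determined by colonoscopy report from the primary care provider at six months".
- Primary outcomes, CRC screening: "CRC screening will be measured primarily by self-report". At six months "participants will be asked whether they had a colonoscopy or any other screening for colorectal cancer during the course of the study". On records, the text reads "participants who report having had CRC screening and records of it will be requested from the health center", a sentence that appears to have lost some words. Men will be asked, at consent, to sign a release so that screening reports can be obtained.

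Other sections show what the trial means by screening.

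- Eligibility criteria: the list of tests includes stool tests ("no Fecal Immunochemical Test (FIT) or Fecal Occult Blood Test (FOBT) in the last 12 months"). The recruitment section repeats the list.
- Patient navigation intervention: navigators meet participants "to assist them with completion of their choice of CRC screening modality". An annual stool test such as FIT "is an acceptable option for colorectal screening in average risk adults aged 50 years and older". Navigators "mail three-day Hemoccult® ICT cards to those who request them". Table 2 lists FIT steps among the navigation tasks.
- Study aims, Sample size and power calculations, and the analysis section on colon cancer screening refer only to CRC screening rates or completed screening, without naming a test or a source.

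**The concern.** A man in the PN arm who chooses FIT, receives a card from his navigator and returns it has done what the intervention asks. He is a success under the CRC screening section and a failure under Outcome assessments. This is one of two primary outcomes, so the estimate and the test of the second primary hypothesis depend on which section is followed.

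The sources conflict as well. One section lets a primary care provider's report decide; the other lets the man's own answer decide and looks to the health center for records. Reliance on a primary care provider also fits poorly with a population that the article calls under-represented in primary care.

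If the choice is left until data are in hand, the result could influence the definition. The Trial status section reports 444 men recruited, with recruitment and follow-up still under way.

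**Working it through.** **1. The two definitions side by side**

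| Feature | Outcome assessments | Primary outcomes, CRC screening |
|---|---|---|
| Tests counted | Colonoscopy | Colonoscopy or any other CRC screening test |
| Deciding source | Provider report | Self-report, primarily |
| Record holder | Primary care provider | Health center |

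Reading the records as verification of self-report would narrow the difference in source. It leaves the difference in tests counted untouched.

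**2. Which definition the rest of the article supports**

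Eligibility and the intervention include stool tests. Aims, power and analysis name screening in general. On tests counted, Outcome assessments stands alone. On source, no other section decides.

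**3. The plan's own power figure**

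Inputs from Sample size and power calculations: 35% against 60%, 90% power, 127 per group, 240 recruited per group, 20% attrition. Alpha is not stated; I assume two-sided 5%.

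n = [1.96·√(2p̄(1−p̄)) + 1.2816·√(p1(1−p1)+p2(1−p2))]² / (p2−p1)², with p̄ = 0.475. This gives 81.8, so 82 per group (90 with continuity correction). The stated 127 is not reproduced from these inputs; at 127 per group, power would be 98.2%. The present point does not depend on this figure.

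**4. Effect of counting colonoscopy only**

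Evaluable men per arm: 240 × 0.80 = 192. Let s be the share of all screens done by FIT. The article gives no value; 20% and 40% are assumptions.

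- Equal share in both arms: MINT rate = 0.35(1−s), PN rate = 0.60(1−s).
- FIT in PN only: MINT rate = 0.35, PN rate = 0.60(1−s).

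Power = Φ[(d − 1.96·SE0)/SE1] + Φ[(−d − 1.96·SE0)/SE1], where d = p2−p1, SE0 = √(2p̄(1−p̄)/192) and SE1 = √((p1(1−p1)+p2(1−p2))/192). Odds ratio = [p2/(1−p2)]/[p1/(1−p1)]. Clustering is ignored.

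| Scenario | MINT | PN | Difference | Odds ratio | Power |
|---|---|---|---|---|---|
| Any test counted | 35% | 60% | 25 points | 2.79 | 99.9% |
| Colonoscopy only, s = 20% in both arms | 28% | 48% | 20 points | 2.37 | 98% |
| Colonoscopy only, s = 40% in both arms | 21% | 36% | 15 points | 2.12 | 91% |
| Colonoscopy only, s = 20% in PN only | 35% | 48% | 13 points | 1.71 | 74% |
| Colonoscopy only, s = 40% in PN only | 35% | 36% | 1 point | 1.05 | 5.5% |

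Worked example, fourth row: p̄ = 0.415, SE0 = 0.0503, SE1 = 0.0499; (0.13 − 1.96 × 0.0503)/0.0499 ≈ 0.63, and Φ(0.63) ≈ 0.74. The second term is negligible except in the last row, where the two terms are 0.040 and 0.015.

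**The case against.** The strongest reply is that the trial does have a recognisable endpoint. Almost everything outside one introductory clause points to completion of any CRC screening test, and the dedicated outcome section says so. Rules for disagreement between self-report and records can reasonably sit in the full protocol or SAP. This stands in part: on tests counted, the problem is one outlying clause, not an endpoint that is missing altogether. But the clause is a definition of a primary outcome, it conflicts with another definition in the same article, and nothing settles the source.

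A second reply is that the low power figures rest on MINT men never using FIT. That is fair. MINT men receive usual counseling on colon cancer screening, and nothing in the article rules out FIT for them. Cards are mailed only in PN, so heavier use there is plausible, but the extent is unknown.

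A reader might also infer more than the article supports:

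- That navigators supply outcome evidence and so tilt the result towards PN. Confirming a colonoscopy or relaying a FIT result is described as an intervention step; the outcome comes from a six-month question put to all participants, plus records.
- That records are never sought for men who deny screening or miss the visit. The sentence on records is garbled and says nothing about these men.
- That every participant signs a release. The article says only that they will be asked.

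**Conclusion.** The two sections contradict each other on tests counted, deciding source and record holder, and must be reconciled. Outcome assessments is the outlier on tests counted. Applied literally, it would miscount completed FIT screens and shrink the PN effect.

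With an assumed FIT share of 20% to 40%, the 25-point difference falls to 20 to 15 points with modest loss of power if the share is equal in both arms. It falls to 13 to 1 points with severe loss only if FIT is confined to PN. The last row of the table is a bound, not an expectation. These figures assume 192 evaluable men per arm, true any-test rates of 35% and 60%, two-sided 5% alpha and no clustering.

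On source, the Randomization section argues that research assistants' knowledge of the arm cannot affect receipt of screening. That does not cover the men's own reporting. They know their arm, so self-report carries a risk of differential over-reporting. This is a risk, not a demonstrated bias.

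**What to change.** Before analysis:

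1. Amend Outcome assessments to agree with the CRC screening section on tests counted: completion of any test on the eligibility list (colonoscopy, flexible sigmoidoscopy, barium enema, CT-colonoscopy, FIT or FOBT) between randomization and six months.
2. State in both sections one deciding source, either self-report or a record from the facility that did the test. Apply it identically in both arms and make the other source a sensitivity analysis.
3. Prefer record confirmation of reported screens in both arms, under the planned releases, because participants are not blinded. Repair the sentence on record requests at the same time.

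The cost is a wording change, plus record requests that the article already foresees for reported screens. The downside of the record rule is that some true screens without a record would not count, possibly unequally by arm: navigators refer PN men to hospitals and relay their FIT results, while MINT men's tests may be spread over unknown sites. For that reason the self-report analysis should be shown beside it. A wider search covering men who deny screening or miss the visit is debatable, since no facility may be known for them, and is not needed to resolve the contradiction.

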#### CRC screening

CRC screening will be measured primarily by self-report. At six-month follow-up, participants will be asked whether they had a colonoscopy or any other screening for colorectal cancer during the course of the study. As the study will be based in the community and not directly related to any specific CRC screening program, participants who report having had CRC screening and records of it will be requested from the health center. Participants will be asked to sign a medical release form at the time of informed consent to grant permission to the research team to obtain CRC screening reports.

### Secondary outcomes

Fruit and vegetable intake will be measured at baseline and six-month follow-up using a two-item questionnaire developed and validated by Resnicow and colleagues
[44]. The items ask how many servings of fruits and vegetables participants eat on an average day.

Physical activity will be measured using the short version of the International Physical Activity Questionnaire (IPAQ-S). The IPAQ-S is a self-report measure that assesses moderate- and vigorous-physical activity, walking, and time spent sitting over a seven-day period. A score is calculated by multiplying the hours and minutes per day spent doing each type of activity by the average metabolic equivalent (MET) and adding each category to the total.

Height, weight and waist circumference will be measured using a stadiometer, with a validated scale (HD-351 Digital Weight Scale; Tanita Corporation of America, Inc.; Arlington Heights, IL, USA), and using a cloth measuring tape, respectively, after the participant has taken off heavy outer garments. All measurements will be recorded to the nearest cm and kg. Height and weight will be used to calculate the body mass index (BMI) for each participant. The difference in weight and waist circumference from baseline to six-month follow-up will be used as a measure of weight-loss over the course of the study. Height will only be measured at baseline.

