		**(selected questions)**
**Medical Comorbidity (Charlson Comorbidity Index)**	**X**	**X**
**Medication adherence (4-Item Morisky Questionnaire)**	**X**	**X**
**International Physical Activity Questionnaire (IPAQ- Short Version)**	**X**	**X**
**Diet (2-Item Food Frequency Questionnaire)**	**X**	**X**
**Intrinsic Motivation (Treatment Self-regulation Questionnaire) (Diet/Physical Activity version)**	**X**	**X**
**Self-Efficacy (Diet/Physical Activity Self-Efficacy Questionnaire)**	**X**	**X**
**Pros and Cons of Colonoscopy**	**X**	**X**
**Fear of Colonoscopy**	**X**	**X**
**Self-Efficacy Regarding CRC Screening**	**X**	**X**
**Intention and Behavioral Control**	**X**	
**Thompson BQ Healthcare Trust Scale**	**X**	**X**
**Assessment of CRC completion screening**		**X**
**Healthy Lifesyle Changes Follow-up Questionnaire**		**X**
**Decisional Regret**		**X**
**Health Literacy (Newest Vital Sign)**	**X**	
**Intervention Satisfaction**		**X**

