2). The men randomized to this group will receive four MINT sessions on lifestyle behaviors. The first MINT session will occur in person immediately after baseline data collection at the barbershop and the subsequent three sessions will occur over the phone. The frequency will be monthly for the first two months and then bi-monthly for the next four months, with each session lasting up to 30 minutes. After the introductory session, each subsequent session will include the following steps: 1) assessing the participant’s motivation and confidence in engaging in a given behavior - physical activity, taking medication as prescribed, smoking cessation, dietary restriction of sodium or increased intake of fruits and vegetables; 2) eliciting barriers and concerns about adoption of each lifestyle modification; 3) summarizing the ‘pros’ and ‘cons’, thereby eliciting positive self-motivational statements about the behavior; 4) providing a menu of options; 5) assessing the participant’s values and goals in connection with his current health behavior pattern; and finally, 6) each encounter will end with a global summary of what was discussed and clarification of an agreed upon action plan.

**Table 2 T2:** Intervention components

	**Motivational interviewing**	**Patient navigation**
Initial Session (in person when possible)	Review lifestyle recommendations in the NHLBI Pamphlets.	Review information in American Cancer Society and Prevent Cancer Foundation DVD/pamphlets:
	• Weight loss for those with a BMI >25	• Colorectal cancer and statistics relevant to black men
	• At least 180 min/week of physical activity	• Risk factors, symptoms and healthy behaviors
	• No more than 1500 mg/day of dietary sodium	• CRC screening options
	• 9-12 daily servings of fruits and vegetables	Explore participant’s barriers (ie lack of knowledge, beliefs and attitudes, fear, logistics) and commitment to CRC screening.
	• 2-3 servings of low fat dairy product	
	• Intake of total fat/saturated fat of < 25% and 75% of total calories respectively	Plan follow-up sessions, colonoscopy referral and/or FIT mailing.
	• Smoking cessation	
	• Medication adherence	
	Barriers to the adoption of TLC are explored and initial goal set.	
Follow-Up/Maintenance Phase (via phone, 30 minutes per session)	1) Assess participant’s motivation and confidence in engaging in given lifestyle behavior	Utilize CEEP (Clarify-Empathize-Explain-Plan) counseling during weekly sessions to assist participants in:

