### Analysis

#### Sample size and power calculations

The sample size is based on the number of participants needed to provide adequate power to test the primary hypothesis, that is, to detect the hypothesized group differences in the primary outcomes. Based on our own clinical experience and estimates from other clinical trials in uncontrolled hypertensive patients
[4-6,11,63] we estimate that the cross-sectional standard deviations (SD) of SBP and DBP at baseline will be about 15/12 mm Hg. Conservatively, assuming (a) that the SD at follow-up will be 25% larger in the MINT group, (b) that the correlation between baseline and follow-up BPs will be 0.6 in the CRC patient navigation group and 0.4 in the MINT group (both due to heterogeneity of treatment response), and (c) that there are no barbershop effects (as this is an individual level intervention) on the change in BP, 200 participants per group will provide 86% power to detect a 5 mmHg differential change in SBP and the same power to detect a 4 mmHg differential change in DBP, based on testing the Time X Group interaction in a MANOVA, allowing for heterogeneous variances and serial correlations
[64]. Regarding the CRC navigation arm, a sample size of 127 participants per group is needed to provide 90% power to detect a group difference in the rate of completed CRC screening at six months from a baseline rate of 35%
[26,27,32,65] to a desired level of 60%. Consequently, we will recruit 240 participants per intervention group (allowing for 20% attrition), which will provide sufficient power to detect the hypothesized difference in both arms of the study. Power analyses were conducted using the R statistical language
[64,66].

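### The stated scoring rule for the secondary physical-activity outcome has no factor for days per week, although the recall window is seven days and MINT's goal is weekly, and it leaves open whether sitting counts

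*Protocol article*

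**What the plan says.** Under Secondary outcomes, the protocol article measures physical activity with the short form of the IPAQ. It says that the instrument "assesses moderate- and vigorous-physical activity, walking, and time spent sitting over a seven-day period". The scoring follows in a single sentence, with this rule: "multiplying the hours and minutes per day spent doing each type of activity by the average metabolic equivalent (MET) and adding each category to the" (the sum over categories). No MET values are given, and the number of days does not appear in the rule.

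Table 1 schedules the questionnaire at baseline and at six months. Table 2, which lists what the MINT sessions recommend, sets the activity goal as a weekly volume: "At least 180 min/week of physical activity".

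The outcome is secondary. The sample size is chosen "to detect the hypothesized group differences in the primary outcomes", and the analyses described in the article cover blood pressure and colorectal cancer screening.

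**The concern.** Weekly activity has three parts: how intense it is, how long it lasts on a day when it is done, and on how many days it is done. The stated rule carries the first two and drops the third. Adding active days is an obvious way for a man to reach a weekly target, and a score built as written would not show it. Because the goal is in minutes per week, a score without days also cannot be read against it.

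The second difficulty is one of definition. Sitting is among the domains listed just before the scoring sentence. The rule speaks of types of activity and then of categories, and does not say whether sitting is one of them. Two analysts could build different totals from the same text.

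At stake is the interpretation of one secondary outcome, on a behaviour that MINT explicitly targets.

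**Working it through.** The article gives no numerical result for this outcome, so there is no figure to reproduce. The check compares the rule as written with the same rule including days.

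**Inputs from the article.** Domains: walking, moderate activity, vigorous activity, sitting. Window: seven days. Rule: time per day × MET, summed. MINT goal: at least 180 min/week.

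**Assumed inputs (the article gives none).** MET of 4 for moderate activity, 3.3 for walking, and 1.0 to 1.5 for sitting.

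**Formulas.** For category c, with t minutes per active day and d days in the week:
- rule as written: S = Σ MET_c × t_c
- weekly volume: W = Σ MET_c × t_c × d_c

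**Step 1: a change in frequency.** Moderate activity, 30 minutes per active day.
- 2 days/week: 60 min/week; S = 30 × 4 = 120; W = 30 × 4 × 2 = 240.
- 6 days/week: 180 min/week, the MINT goal; S = 30 × 4 = 120; W = 30 × 4 × 6 = 720.

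Weekly volume triples and S does not move. The MET value cancels, so this holds for any weight.

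**Step 2: ranking of two men.** Moderate activity only.
- 60 minutes on 1 day: S = 60 × 4 = 240; W = 60 × 4 × 1 = 240.
- 30 minutes on 7 days: S = 30 × 4 = 120; W = 30 × 4 × 7 = 840.

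S puts the first man at twice the second. On weekly volume the second is at 840/240 = 3.5 times the first. Both ratios are again free of the MET value.

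**Step 3: does an averaging reading remove the problem?** If time per day meant the average over all seven days, S would equal W/7. The two cases in Step 1 would score 240/7 = 34.3 and 720/7 = 102.9, and the order in Step 2 would be right. The article does not state this reading.

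**Step 4: what turns on sitting.** Man A sits 12 h (720 min) and does nothing else. Man B sits 6 h (360 min), with 30 min of moderate activity (30 × 4 = 120) and 30 min of walking (30 × 3.3 = 99), so 219 from activity.

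| | A | B |
|---|---|---|
| Sitting left out | 0 | 219 |
| Sitting added, MET 1.0 | 720 | 360 + 219 = 579 |
| Sitting added, MET 1.5 | 1080 | 540 + 219 = 759 |

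The order of A and B depends entirely on a choice that the sentence does not make.

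**Step 5: direction of change within one man, if sitting were added.** Man A replaces 60 min of sitting with B's 60 min of activity. At MET 1.0 his score goes from 720 to 660 + 219 = 879. At MET 1.5 it goes from 1080 to 990 + 219 = 1209. In this exchange the score still rises.

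**The case against.** The strongest defence is that this is a journal article paraphrasing the scoring of a named, standard questionnaire. It mentions the seven-day window one sentence earlier, and nothing shows that the investigators would ignore days when they score it. Item-level scoring is commonly left to the full protocol or the SAP. This has weight, and the averaging reading in Step 3 would rescue the rule. But the article does not leave scoring to another document. It states a formula, and that formula, followed as written, drops days. This is a misstated rule, not an omitted detail.

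Several stronger conclusions are tempting and do not stand:

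- *Sitting is added to the total.* A reader might infer this because sitting is in the preceding list. But the rule multiplies time in each type of activity, and the categories then summed can be read as those types. Sitting is given no MET weight. Inclusion is one reading, not an established fact, so the placing of a sedentary man above an active one through sitting is not established either.
- *A real effect could be reversed.* Step 5 shows the score rising when activity replaces sitting minute for minute, even with sitting included. A comparison of two different men does not show that a randomised contrast would change sign.
- *The score misses what MINT targets.* It still responds to minutes per day and to intensity. What it loses is frequency.
- *Power is lost.* Any figure would need standard deviations, an effect size and MET weights that the article does not give, and the larger losses would also require sitting to be in the total.
- *The mechanism of a blood-pressure effect would be misread.* No mediation analysis is described.

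**Conclusion.** The point holds for days. As stated, the rule cannot register how often a man is active and can misrank men on weekly volume. In the examples, a threefold difference in weekly volume leaves the score unchanged, and a 3.5-fold advantage appears as a score half as large. These ratios do not depend on the MET assumption. They do depend on reading time per day as time on an active day, not as a seven-day average.

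On sitting, the finding is only that the text is ambiguous and needs to be settled.

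The consequence is limited to one secondary outcome. The primary analyses and the sample size are untouched, and no power claim attaches to the point.

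**What to change.** Replace the scoring sentence with a definition along these lines: physical activity is scored in MET-minutes per week, as the sum over walking, moderate and vigorous activity of MET × minutes per day × number of days in the past seven days. Sitting time is reported separately and is not part of the total.

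The cost is one sentence of analysis wording. The questionnaire is already scheduled at both visits, so no added visit is needed. The change assumes that the form records the number of days for each activity. The article does not say so, and the sponsor should confirm it against the case report form. If the full protocol or SAP already scores the instrument this way, only the article's description needs to be corrected.
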